#### HEALTH CARE EFFICIENCY PROBLEM

Structured follow-up care according to nationally approved BETER screening guidelines for late adverse treatment effects for adult lymphoma survivors was first introduced in 2013-2014 in 5 BETER clinics. Currently ~1,900 survivors have visited one of the 18 BETER clinics.

However, the efficiency of the BETER clinics has not yet been evaluated. There is a real gap in knowledge about (cost-)effectiveness of cancer survivorship programs in clinical practice (see Systematic Review). Existing studies only evaluated the yield of late effects in such programs, without a comparison group, or simulated health benefits in hypothetical cohorts (see Systematic Review). Yet, we are currently attempting to establish BETER survivorship care in all Dutch hospitals participating in BETER. The current situation with absence of BETER survivorship care in a substantial number of hospitals still allows for the conduct of a quasi-experimental study to evaluate effectiveness of BETER survivorship care. Once full nationwide implementation is in place, evaluation as proposed in this project will no longer be possible.

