
#### 1.7.2. Sample size calculation

In the 'intention to screen' analysis, we expect a 5-year accumulation of 0.78 DALYs in the intervention group and 1.18 DALYs in the control group. With a 2-sided significance level of 0.05 and 80% power to detect a difference of 0.20 standard deviation (small effect size) and larger, we need 393 patients in each study arm. When we take 15% loss to follow-up and incomplete data into account, we need 452 patients in each study arm.

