### 1.8. DATA-ANALYSIS

#### 1.8.1. Intention to screen analysis

To assess the impact of BETER survivorship care on the centres' eligible lymphoma population, the outcome parameters will be compared between the first 450 survivors who were invited to a BETER clinic that started in 2013-2014 and 450 matched survivors who were treated for lymphoma at BETER centres that does not start a clinic until 2021-2024. Reasons why participating centres did not start a BETER clinic before 2021 are of logistic nature involving identification and tracing of patients and setting up the infrastructure, especially the availability of an interested cardiologist and a nurse-practitioner; factors very unlikely to be associated with treatment-specific risks of late effects and our study outcomes. Centres starting an early BETER clinic included both University Medical Centres and large peripheral hospitals. This allows us to use an instrumental variable analysis with the variable 'treated for lymphoma at a centre with a BETER clinic that started in 2013-2014' (y/n) as instrumental variable. We hereby mimic randomization and minimize the risk of bias in this observational study. The variable 'treated for lymphoma at a centre with a BETER clinic that started in 2013-2014' is strongly associated with the likelihood of

receiving the intervention (65% vs. 0-5% for clinics that started in 2013-2014 and 2021-2024 respectively), but not associated with any prognostic factor or with the outcome (other than through the intervention). The attendance rates are based on preliminary data from a small study in a few BETER clinics which showed that the attendance rate was 60-70% and that survivors only rarely visited a BETER centre not connected to their original lymphoma treatment centre. Individual matching of control group participants to the intervention group on relevant treatment characteristics will control for any differences in lymphoma treatment between centres.

When we select the matched comparison group eligible for BETER care in 2013-2016, we do not yet know whether they will attend the BETER clinic when invited in 2021-2024; therefore, in a truly unbiased analysis, attendance should not be an eligibility criterion in the intervention group as well. Our intention-to-screen analysis is therefore the most valid approach to evaluation of the cost-effectiveness of BETER survivorship care.

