#### 1.8.2. Patient level analysis

To assess the impact of BETER survivorship care on screened/treated individuals, outcome parameters will be compared between the first 270 survivors who attended a BETER clinic that started in 2013-2014 and matched survivors who are not (yet) screened and were treated for lymphoma at BETER centres that start a clinic in 2021-2024.

On both levels of analysis, multiple linear regression analysis will be used for continuous outcomes (such as DALYs and health care costs) and Poisson or negative binomial regression analysis will be used for count variables (i.e. yield of previously undiagnosed adverse events). The regression analyses will also take the amount of follow-up time into account, thereby correcting for a possible difference in follow-up time in the intervention and control group.

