#### 2.4. Cost-effectiveness Analysis

The cost-effectiveness analysis will be performed by means of a discrete event simulation, to take the factor "timing" into account and because patient level data is available. In the cost-effectiveness analysis, we will incorporate several scenarios for follow-up strategies, based on the data generated in the proposed study. The results of the cost-effectiveness analysis will be incremental costs (or savings) of the BETER care per QALY gained. The CEA will be performed according to the guidelines for economic evaluations of the Dutch Zorg Instituut. State of the art health economic methods will be applied. Uncertainty around the results will be quantified by means of non-parametric bootstrapping and cost-effectiveness acceptability curves, showing the possibility of the BETER care being whether or not cost-effective for various values of the Dutch society willingness to pay for one QALY.

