## 6. REQUESTED PERSONNEL

The project coordinator (0.2 FTE for 4.5 years) will coordinate the project, involving communication with all parties involved and coordination of data collection and analysis. This requires excellent coordination skills since many parties and different stakeholders are involved (12 different hospitals with haemato-oncologists, radiation oncologists, nursing specialists and cardiologists, the patient organisation, five disease registries and the survivors' general practitioners). The coordinator will also

obtain Medical Ethics approval in all 12 hospitals and organise research contracts according to GDPR rules.

A PhD student will perform part of the data collection from the medical records (20%), perform quality control with the data abstractor, send letters to general practitioners, perform all linkages with disease registries, and analyse the yield and effectiveness data as well as attendance and adherence data.

A data abstractor (1 FTE for 2.75 year) will perform most of the data collection (abstraction of 80% of the medical records) and assist the PhD student in sending letters to general practitioners.

A junior health technology assessment researcher will perform the (cost-)effectiveness analysis (1 FTE for 0.5 year) under supervision of a senior health technology assessment researcher (0.2 FTE for 0.5 year).

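### Groups are formed by treating centre, but the sample size and the named regressions make no allowance for clustering, so the stated 80% power and 5% error hold only if the between-centre ICC is zero

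*Protocol*

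**What the plan says.** **Allocation.** Under 1.2.2 and 1.2.3, a survivor belongs to the intervention group if the original treatment centre was already inviting patients in 2013-2016, and to the control group if that centre opens its clinic only in 2021-2024. Section 1.8.1 uses the same centre-level fact as the instrument: "treated for lymphoma at a centre with a BETER clinic that started in 2013-2014' (y/n) as instrumental variable". An early centre cannot also be a late one, so no hospital contributes to both groups.

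**Number of centres.** The section on the health care efficiency problem says that structured care "was first introduced in 2013-2014 in 5 BETER clinics". Section 6 refers to "12 different hospitals with haemato-oncologists, radiation oncologists, nursing specialists and cardiologists". The number of control centres is not stated; 12 − 5 gives about 7.

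**Sample size.** Section 1.7.2 works "With a 2-sided significance level of 0.05 and 80% power" and concludes: "80% power to detect a difference of 0.20 standard deviation (small effect size) and larger, we need 393 patients in each study arm". The only inflation is 15% for loss and incomplete data, giving 452. The Summary repeats the claim, section 8.1 relies on it, and 1.7.3 extends the same reasoning to the patient-level analysis.

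**Analysis.** Section 1.8.2 states: "On both levels of analysis, multiple linear regression analysis will be used for continuous outcomes (such as DALYs and health care costs". It names Poisson or negative binomial regression for counts and adds follow-up time to the models. No centre effect or clustered variance appears.

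**Cost-effectiveness.** Section 2.4 says: "Uncertainty around the results will be quantified by means of non-parametric bootstrapping". It names no resampling unit.

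**The concern.** When whole hospitals are either exposed or unexposed, the comparison rests on about a dozen hospitals, however many patients each one supplies. Patients of one hospital can share cardiology input, referral habits and screening practice, so their outcomes may be correlated. An ordinary regression on patients then understates the standard error of the group difference, and a chance difference between a few hospitals can pass for an effect of BETER care.

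The protocol itself gives reason to expect some between-centre variation. The section on practice variation reports that active clinics differ substantially in how often and how much they test. Section 1.8.1 says that centres differed in access to an interested cardiologist and a nurse-practitioner, and that the early starters were a mix of university and large peripheral hospitals.

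The results are meant to support national implementation, or adaptation or withdrawal of guidelines, so intervals that are too narrow would matter.

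**Working it through.** **Inputs from the protocol:** two-sided α 0.05, 80% power, 0.20 SD, 393 per arm, 15% loss (1.7.2); 5 early clinics (health care efficiency problem); 12 hospitals (section 6).

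**Assumptions:** 7 late centres (12 − 5), equal centre sizes within each arm, 393 analysable per arm, and one ICC for both arms. The ICC is not in the protocol, so it is shown as a range.

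**Step 1: reproduce the plan's figures.**
- n = 2(1.96 + 0.8416)² / 0.20² = 392.4, so 393 per arm (power 80.06%).
- 393 × 1.15 = 451.95, so 452.
- Patient level (1.7.3): 0.65 × 452 / 1.07 = 274.6; detectable difference 2.8016 × √(2/274) = 0.239 SD.

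All agree with the protocol, so its power figures contain no allowance for clustering.

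**Step 2: add clustering.**
- Centre sizes: 393/5 = 78.6 (early) and 393/7 = 56.1 (late).
- Design effect per arm = 1 + (size − 1) × ICC; V is the mean of the two arms.
- SE of the difference, in SD units = √(2V/393).
- Power (z) = Φ(0.20/SE − 1.96).
- Type I error of the uncorrected test = 2[1 − Φ(1.96/√V)].
- Power (t) uses a noncentral t on 5 + 7 − 2 = 10 df.

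Example at ICC 0.01: the design effects are 1.78 and 1.55, so V = 1.66 and SE = 0.092. Power = Φ(0.20/0.092 − 1.96) = 58.5%, and type I error = 2[1 − Φ(1.96/1.29)] = 12.9%.

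| ICC (assumed) | V | Power, z | Power, t on 10 df | Uncorrected type I error |
|---|---|---|---|---|
| 0 | 1.00 | 80.1% | 71.5% | 5.0% |
| 0.001 | 1.07 | 77.5% | 68.7% | 5.8% |
| 0.005 | 1.33 | 68.1% | 59.2% | 8.9% |
| 0.01 | 1.66 | 58.5% | 50.1% | 12.9% |
| 0.02 | 2.33 | 45.1% | 38.3% | 19.9% |
| 0.05 | 4.32 | 27.1% | 23.0% | 34.6% |

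The z column isolates the effect of clustering. The t column also includes the cost of having only 12 centres, which is present even at ICC 0.

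**Step 3: check by simulation.** With 20,000 runs per ICC, the uncorrected test rejected a true null in 4.9% of runs at ICC 0, 13.2% at 0.01, 19.9% at 0.02 and 34.7% at 0.05.

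**Step 4: can more patients repair it?** Equivalently, SE² = 2(1 − ICC)/n + ICC(1/5 + 1/7). On the z reference, 80% power for 0.20 SD needs 421 analysable per arm at ICC 0.001, 589 at 0.005 and 1,188 at 0.01. As n grows, SE² cannot fall below 0.343 × ICC, while 80% power requires SE² ≤ (0.20/2.8016)² = 0.0051. Above an ICC of about 0.015, no number of patients in these 12 centres is enough.

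**The case against.** **Details may sit in a separate analysis plan.** The variance estimator and the resampling unit are often left to that document, and each named regression can be fitted with clustered errors. A reader might infer that the protocol prescribes an unclustered bootstrap. It does not: section 2.4 is silent on the unit. This part of the objection stands, and for the bootstrap the point is only that the unit should be named. The objection does not reach the sample size. The protocol itself states the power, and correcting standard errors later would not make that figure right.

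**The residual ICC may be small.** Matching covers sex, age, year of diagnosis and treatment exposures. Events come largely from national registries and general practitioners, costs largely from standard tariffs, and disability weights from the literature. Controls were usually discharged at five years, so the original centre often does not manage their later care. These are fair reasons to expect a low value, perhaps lower among controls than the single ICC used here. None shows that it is zero.

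**Section 1.8.1 defends the design.** It argues that late starts had logistic causes and that matching removes treatment differences between centres. Both arguments concern bias. Even hospitals allocated at random would need inference that respects the hospital.

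**The centre count is constructed.** The figure of 12 appears in a description of coordination workload, and the 7 late centres and equal sizes are inferred. That is correct, so the table is illustrative.

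**Conclusion.** The point holds. The stated 80% power for 0.20 SD, and a 5% error rate under the regressions as named, are correct only at a residual between-centre ICC of zero. The firmest anchor is 1.7.2, whose 393 reproduces exactly under independence.

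The size depends on an ICC that the protocol does not give. At 0.001 the effect is modest; from about 0.005 upward it is material.

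Two stronger conclusions are tempting but unsupported:
- **That true power is well below 80%.** On the z reference this is not so at ICC 0.001. The lower figures on 10 df come partly from the choice of reference distribution.
- **That the study is underpowered for the effect it expects.** The expected difference is 0.40 DALY, and no SD for DALYs is given. It equals 0.20 SD only if the SD is 0.40/0.20 = 2.0, so power for that difference cannot be derived.

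**What to change.** - **Section 1.7 (and the Summary and 8.1):** state the number of early and late centres and give power as a range over ICC from 0 upward, with the reference distribution named. Ideally estimate the ICC from the existing 27-centre cohort. Treat the patient-level figure in 1.7.3 the same way.
- **Section 1.8:** specify centre-level inference with a small-sample correction for every group comparison at both levels, including the instrumental variable analysis. For continuous outcomes, use a random centre intercept with Kenward-Roger or Satterthwaite degrees of freedom; alternatively, use CR2 cluster-robust errors with Satterthwaite degrees of freedom.
- **Section 2.4:** state that the bootstrap resamples centres first and then patients within centres.

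The cost is protocol wording and slightly more complex code, together with wider intervals and a less favourable stated power. No extra patients are proposed. The change makes the inference honest but does not restore 80% power; if that is wanted, adding centres helps more than adding patients within the same ones.

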#### 1.2. PATIENT (P)

##### 1.2.1. Patient population

The study will be nested in a large nationwide retrospective cohort study of HL survivors treated in 27 Dutch centres between 1965 and 2012 (15,16). This cohort was originally established in the 1980s-1990s to examine the late effects of HL treatment; since then the cohort has been periodically extended with more treatment centres, patients diagnosed in more recent years and with diffuse large B-cell lymphoma (DLBCL) survivors diagnosed between 1989 and 2012. Lymphoma survivors eligible for BETER survivorship care were successfully treated at least 5 years ago for HL or DLBCL at age 15-60 years and are less than 70 years of age at invitation. The patient population in this evaluation study will only consist of HL survivors eligible for BETER survivorship care, as they were the first to be invited to the BETER clinics in 2013-2016 due to their higher risk of late adverse treatment effects compared to DLBCL survivors.

1.2.2. Intervention group: the first 450 HL survivors between 2013 and 2016 who were invited for screening for late adverse treatment effects in the BETER centre where they were originally treated for HL. With attendance rates ranging between 60-70%, around 300 HL survivors in the intervention group are expected to receive screening at the BETER clinics.

1.2.3. Control group: frequency matched group of 450 HL survivors, eligible for BETER screening for late adverse treatment effects in 2013-2016, but not yet invited because the centre where they were originally treated for HL does not start a BETER clinic until 2021-2024. So, the control group will be invited in 2021-2024.

Controls will be matched with the intervention population on the following criteria:

- sex
- age at diagnosis ( $\pm 3$  years)
- year of diagnosis ( $\pm 3$  years)
- lymphoma treatment characteristics associated with increased risk of CVD, breast cancer, hypothyroidism and functional asplenia (see also 1.3.1.). In practice this implies matching on chest radiotherapy (y/n), neck radiotherapy (y/n), spleen radiotherapy (y/n), splenectomy (y/n) and anthracyclines (y/n + doxorubicin  $\approx 300$  mg/m^2 y/n).

Survivors selected as controls should be alive at the time the corresponding survivor in the intervention group was invited to

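### Controls are matched on sex, age, year of diagnosis and treatment, but the regressions name only follow-up time as an adjustment; the matching factors should enter the models and the type of matching should be reconciled

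*Protocol*

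**What the plan says.** Protocol section 1.2.3 states: "Controls will be matched with the intervention population on the following criteria". The list that follows has sex, age at diagnosis within 3 years, year of diagnosis within 3 years, yes/no items for chest, neck and spleen radiotherapy and for splenectomy, and two anthracycline items (any use, and a dose threshold).

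The type of matching is described in two ways. Sections 1.1 and 1.2.3 call it frequency matching. Section 1.8.1 calls it individual: "Individual matching of control group participants to the intervention group on relevant treatment characteristics will control for any differences in lymphoma treatment between centres". Sections 1.2.3 and 8.5.1 also refer to a corresponding intervention survivor for each control, which suggests pairs.

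Section 1.7.2 sizes the study: "With a 2-sided significance level of 0.05 and 80% power" for a difference of 0.20 SD, "we need 393 patients in each study arm", raised to 452 for 15% loss and incomplete data.

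Section 1.8.2 covers both the intention-to-screen and the patient-level analysis. It says "multiple linear regression analysis will be used for continuous outcomes (such as DALYs and health care costs"), with Poisson or negative binomial models for counts, and adds: "The regression analyses will also take the amount of follow-up time into account". No matching factor and no pair or set term is named. Section 8.3.1 tells the funder that the matching makes the comparison of quality of life and productivity valid; both are measured once, without a baseline.

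**The concern.** Matching in a cohort forces the two arms to be alike on factors that predict the outcome. The variance of the between-arm difference then falls, but a model without those factors does not see the fall and reports a standard error that is too large. The precision that the matching was meant to buy is lost.

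A caliper also reduces imbalance without removing it. Start of follow-up corresponds between the arms (section 1.5), so age at the start depends on both age at diagnosis and year of diagnosis. Age matters for the primary outcome by construction, because years of life lost use the life expectancy at the age of death (section 1.6.1.2). Loss of survivors after selection can disturb the balance further. If the models leave these factors out, whatever imbalance remains is counted as an effect of BETER care.

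This touches DALYs, costs and event counts at both levels of analysis, and any quality-of-life or productivity score analysed as a continuous outcome. The unsettled type of matching matters too, because the correct variance depends on whether there are pairs.

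**Working it through.** **Inputs from the protocol.** Two-sided alpha 0.05, power 80%, difference 0.20 SD, 393 per arm, 15% loss (1.7.2); calipers of ±3 years on age and on year of diagnosis (1.2.3).

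**Inputs assumed, because the protocol gives none.** The within-match correlation of the outcome, rho (0.05 to 0.50), and the slope of the outcome on age (0.01 to 0.02 SD per year). Under frequency matching, read rho as the share of outcome variance explained by the balanced factors; the same formulas then apply approximately.

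**1. Reproduce the plan's figure.** n = 2 × ((1.960 + 0.842)/0.20)² = 392.6, so 393 per arm. 393 × 1.15 = 451.95, so 452. Both match. This is the formula for two independent samples, with no allowance for matching.

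**2. Effect of ignoring the matching, without imbalance.**
- Reported SE divided by true SE = 1/√(1 − rho)
- True alpha = 2 × (1 − Φ(1.96/√(1 − rho)))
- Power, factors ignored = Φ((0.20/√(2/393) − 1.96)/√(1 − rho))
- Power, factors used = Φ(0.20/√(2(1 − rho)/393) − 1.96)
- Matched pairs needed for 80% power = 2(1 − rho) × ((1.960 + 0.842)/0.20)²

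| rho (assumed) | SE too wide by | True alpha | Power, ignored | Power, used | Pairs needed |
|---|---|---|---|---|---|
| 0 | 0% | 5.0% | 80.1% | 80.1% | 393 |
| 0.05 | 2.6% | 4.4% | 80.7% | 82.0% | 373 |
| 0.10 | 5.4% | 3.9% | 81.3% | 84.0% | 354 |
| 0.20 | 11.8% | 2.8% | 82.7% | 88.0% | 314 |
| 0.30 | 19.5% | 1.9% | 84.3% | 91.8% | 275 |
| 0.50 | 41% | 0.6% | 88.4% | 97.8% | 197 |

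The requirement never exceeds 393 for rho at or above zero. DALYs driven by rare events may lie at the low end of the range.

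**3. Imbalance inside the calipers.** The largest gap in age at the start of follow-up between two matched survivors is 3 (age at diagnosis) + 3 (year of diagnosis) = 6 years. That bounds one pair; it is not an expected difference between arms. Bias equals slope × mean gap. A mean gap of 1 year gives 0.01 to 0.02 SD, or 5-10% of the 0.20 SD target. If every control were 3 years off in the same direction, it would be 0.03 to 0.06 SD, or 15-30%.

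How large a mean gap is likely? An illustrative simulation drew controls at random within ±3 years of age at diagnosis (450 survivors, a pool of 1,500, age SD 10 years). The mean gap left was about 0.00, 0.06 and 0.19 years when the source pools differed by 0, 2 and 5 years. At 0.02 SD per year the largest of these is 0.19 × 0.02 = 0.004 SD. The simulation covers neither the year-of-diagnosis caliper nor later loss.

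**4. Cost of adjustment.** Sex 1, age 1, year 1, three radiotherapy items 3, splenectomy 1, anthracyclines 2: 9 degrees of freedom, against 2 × 393 = 786 survivors.

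**The case against.** The strongest reply is that the protocol never says the matching factors are left out. Section 1.8.2 speaks of multiple regression that also takes follow-up time into account, and both words leave room for covariates. A covariate list often sits in the statistical analysis plan, which is not at hand. This stands as far as it goes: the point is conditional on omission. But the protocol does fix the models for both levels and names one adjustment, and sections 1.8.1 and 8.3.1 rest comparability on the matching (with, in 1.8.1, the claimed instrument). Naming the factors is therefore more than housekeeping.

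Second, frequency matching creates no pairs, so a two-sample calculation is acceptable. That is right for the sizing. It does not remove the need for the matching factors in the model, and it does not resolve the conflict with section 1.8.1.

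Third, the sentence in 1.8.1 about what matching controls concerns only differences in lymphoma treatment. It should not be read as a claim about age or calendar year. The instrumental variable argument there would not by itself remove an age difference between early and late centres.

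Two stronger readings are tempting. A reader might infer that the study is underpowered or prone to false positives because the matching is ignored; the table shows the opposite. A reader might also infer serious bias. If controls were on average 1.3 years older (age SD 10 years, age explaining 10%, 20% or 50% of outcome variance), the effect would be off by 0.04, 0.06 or 0.09 SD and the false-positive rate would be about 7%, 11% or 19%. No passage suggests such a one-directional lean, section 1.8.1 attributes late starts to logistics, and random selection within the calipers leaves far less.

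**Conclusion.** The point holds in a limited form. If the matching factors are left out of the regressions in 1.8.2, standard errors are too wide under either kind of matching. The consequence is a conservative test and lost precision: for assumed rho of 0.05 to 0.30, true alpha is 4.4% to 1.9%, and power at 393 per arm is 81-84% where 82-92% was available. Residual age or year imbalance would also stay in the effect estimate. That bias is probably small, and the documents do not allow it to be sized. Rho and the age slope are assumptions throughout. The 393 and 452 per arm are sufficient on this ground. Separately, the protocol contradicts itself on whether matching is by frequency or individual, and this has to be settled before the variance can be specified. Adjustment is worth making because it gains precision and guards against imbalance at almost no cost.

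**What to change.** In section 1.8, state that every between-arm regression (linear, Poisson and negative binomial, at both levels) includes sex, exact age at diagnosis, exact year of diagnosis, and the indicators for chest, neck and spleen radiotherapy, splenectomy and anthracyclines, alongside follow-up time. Keep all survivors, including those whose match is lost; a pairs-only test would discard the partner of each lost survivor.

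Reconcile the matching type across 1.1, 1.2.3 and 1.8.1. If it is individual, add a matched-set term or cluster-robust standard errors. In 1.8.1, say that treatment differences are handled by matching together with regression adjustment.

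The cost is a few sentences and about 9 degrees of freedom. The variables are matching criteria drawn from the existing cohort data set (1.1, 1.2.3), so no extra patients or data collection are needed, and the sample size stays as it is.
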